**Biochemistry**

Biochemical analysis of complexes I-IV will be performed from immediately frozen muscle tissue according to standard procedures.

**FACS analysis**

FACS analysis of CD34+ and CD133+ circulating hematopoietic progenitor cells will be performed twice a week from peripheral blood.

**Phosphor 31 Magnetic Resonance Spectrosopy**

All FRDA patients are subjected to phosphor 31 magnetic resonance spectrosopy (31P MRS) of the left leg during an incremental exercise protocol at 2, 4 and 6 W. By measuring the PCr kinetics and calculating the time constants, mitochondrial function can be quantitated.

# **31P MRS Protocol**

The spectroscopic measurements are performed on a 1.5 Tesla whole body MR scanner (Magnetom Magnetom Avanto, Siemens Erlangen, Germany) by using a circular polarized double resonator surface coil that permits the receipt of 1H resonances at 63.5 MHz and 31P resonances at 25.8 MHz. The transmitter coil has a diameter of 21 cm, the receiver coil has a diameter of 14 cm. A free induction decay (FID) sequence with following parameters is employed: repetition time (TR), 1000 ms; echo time (TE), 0.13 ms; flip angle, 90°; 10 averages; acquisition time (TA), 10 s. The nuclear Overhauser enhancement (NOE) is applied to all spectroscopic measurements. The signal is received from the calf that is fixed on the double resonator coil. The other leg is embedded above the depth range of this coil.

### 31P MRS Data Analysis

The spectral data are processed using the commercial software package as provided by the manufacturer (Siemens Erlangen, Germany). The peak areas of PCr are fitted in the frequency domain. In addition, the position of the peaks of PCr and Pi are determined. Since absolute concentrations are not calculated, the integrals of the metabolite peaks are not corrected for partial saturation and the NOE effects. Moreover, we assume that the T1 relaxation times of the metabolites are constant throughout each 31P MRS session [30;31]. The total extent of PCr hydrolysis is determined by normalization of the end-exercise integral to the baseline integral at rest. The intracellular pH is calculated from the chemical shift of Pi based on the equation: [Taylor et al., Mol.Biol.Med. 1983]

pH=6.75 + log(-3.27)/(5.69-) (1)

 is the chemical shift of the Pi peak in parts per million (ppm) relative to PCr.

The time constants  and PCrss values, meaning the difference between baseline and steady-state PCr level are calculated for each workload increment by using a non-linear regression analysis in SPSS 15.0 for windows (SPSS Inc., Chicago, Illinois, U.S.A.), as previously reported [Nevill et al., JAP 1997]. For that purpose, the last PCr integral of the preceding increment or rest phase is considered baseline PCr integral for the following increment and for data normalization. The time constants  and PCrss values are iteratively calculated by using the equation: [Schocke Invest Radiol 2006, Greiner JVS 2006, Esterhammer Mol.Imaging.Biol. in press]

PCr(*t*) = PCr0 -/+ PCrss [1-*e-t*/] (2)

PCr0 is the baseline value, PCr(*t*) the PCr value at the time (*t*) and PCrss the difference between baseline PCr value and the estimated steady-state level. The coherence between the mono-exponential model and the data of each subject is described by a coefficient of determination r2: [Schocke Invest Radiol 2006, Greiner JVS 2006, Esterhammer Mol.Imaging.Biol. in press]

r2 = 1 - residual sum of squares / corrected sum of squares (3)

A coefficient r2 above 0.4 is considered an acceptable fit, whereas a coefficient r2 below 0.4 indicated a weak agreement with a monoexponential model and rather progressive PCr breakdown.

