**The aims of the proposed study are**

1) to investigate morphological and biochemical parameters of skeletal muscle systematically, to identify the amount of CD34+ and CD133+ hematopoietic progenitor cells as well as to measure the Frataxin expression in skeletal muscle biopsies of FRDA patients at baseline.

2) to measure numbers of circulating CD34+ and CD133+ hematopoietic progenitor cells in peripheral blood of FRDA patients during treatment with rhuEPO;

3) to study effects of EPO treatment on Frataxin expression, numbers of CD34+ and CD133+ hematopoietic progenitor cells, satellite cells, capillary density and respiratory chain complex activities of skeletal muscle tissue obtained by re-biopsy.

4) Magnetic resonance spectroscopy in skeletal muscle at baseline and study endpoint will be additionally performed to analyze *in-vivo* changes in muscle energy metabolism.

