**Patients and Investigations**

Seven adult subjects with definite FRDA will be enroled in this study. Skeletal muscle will be obtained by an open biopsy from at baseline (untreated) and after 2 months of rhuEPO treatment after written informed consent.

Treatment encompasses rhuEPO 3.000 IU (~100 IU/kg KG) three times weekly subcutaneously for 8 weeks.

Specimen from the quadriceps muscle and MR spectroscopy from the contralateral side will be obtained pre- and post rhuEPO treatment.

Frataxin-levels will be assessed in lymphocytes and muscle specimen at baseline and study end-point. Furthermore, FACS analysis of circulating CD34+ and CD133+ cells in peripheral blood will be perfomed bi-weekly. The numbers of CD34+ and CD133+ cells and capillary density per mm2 will be quantified in skeletal muscle at baseline and after 8 weeks EPO treatment.

Biochemically, complex I, II, and III of the respiratory chain in the quadriceps muscle will be evaluated pre-and post treatment.

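### Total PCr hydrolysis is read at end-exercise without a fixed workload, so this one MRS measure may not be comparable between baseline and week 8

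*Protocol*

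**What the plan says.** Aim 4 of the Protocol is a before/after comparison: "Magnetic resonance spectroscopy in skeletal muscle at baseline and study endpoint will be additionally performed". The section Phosphor 31 Magnetic Resonance Spectrosopy puts all patients through spectroscopy "of the left leg during an incremental exercise protocol at 2, 4 and 6 W". The same section names the measure meant to capture mitochondrial function: "By measuring the PCr kinetics and calculating the time constants, mitochondrial function can be quantitated".

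The section 31P MRS Data Analysis then sets out two kinds of measure.

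- **Total depletion.** "The total extent of PCr hydrolysis is determined by normalization of the end-exercise integral to the baseline integral at rest". No workload is named.
- **Step-specific measures.** The time constants and the steady-state PCr differences are "calculated for each workload increment by using a non-linear regression analysis in SPSS 15.0 for windows". For these, "the last PCr integral of the preceding increment or rest phase is considered baseline PCr integral for the following increment".

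The three 31P MRS sections give no rule for a step that is not completed, or for a patient who reaches a different step at the two visits. On numbers, Patients and Investigations says "Seven adult subjects with definite FRDA will be enroled in this study", while Number of patients gives 5 to 7. There is no control group.

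**The concern.** In an incremental test, the fall in PCr from rest to the end of exercise depends on how many steps were done as well as on how the muscle handles each step. The loads are absolute and are not scaled to the patient's capacity. The Scientific background describes leg weakness and wasting, lower-limb spasticity and eventual wheelchair use. The inclusion and exclusion criteria set no strength or walking requirement. It is therefore plausible that some patients will not finish 6 W on one or both occasions.

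If the last completed step differs between visits, the definition compares two different amounts of work. A patient who gets further at week 8 shows extra depletion that comes from the extra step. A patient who stops sooner shows less depletion with no metabolic gain. In an uncontrolled comparison of 5 to 7 patients, a few such cases can weigh on the mean.

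**Working it through.** The Protocol gives no numerical result for this measure, so there is no figure to reproduce. What follows is an illustration.

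**Inputs from the Protocol:** three steps (2, 4 and 6 W); 7 patients (also given as 5 to 7); depletion read at end-exercise relative to rest.

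**Assumptions, not in the Protocol:** each step lowers PCr by the same amount d, in points of resting PCr (range 5 to 20); treatment reduces the fall per step by a true fraction r; some patients complete 4 W at baseline and 6 W at week 8, and the rest complete 6 W at both visits.

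**One patient.** Depletion after k steps is kd before treatment and kd(1 − r) after.

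- Same steps, 6 W at both visits, d = 15, r = 20%: 3 × 15 = 45 before and 45 × 0.8 = 36 after. The direction is correct.
- 4 W before, 6 W after, same patient: 2 × 15 = 30 before and 36 after. The direction is reversed. At a matched 4 W the values are 30 and 24.

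**Break-even.** From 4 W to 6 W, depletion rises when 3d(1 − r) > 2d, that is when r < 1/3.

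| Steps completed, before to after | Break-even r, equal falls | Break-even r, each fall a fraction of the preceding level (5 to 20%) |
| --- | --- | --- |
| 2 to 3 | 33% | 31 to 33% |
| 1 to 2 | 50% | 47 to 49% |
| 1 to 3 | 67% | 64 to 66% |

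For 2 to 3 steps with d = 15, baseline depletion is 30 points. The week 8 value is 40.5 at r = 10%, 36 at 20%, 31.5 at 30% and 27 at 40%. The reversal is real for modest improvements but not automatic.

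**Group mean, 7 patients, m of whom go from 4 W to 6 W.**

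- As written: [(7 − m)(−3dr) + m(d − 3dr)]/7 = d(m − 21r)/7.
- At matched workload: [(7 − m)(−3dr) + m(−2dr)]/7 = −dr(21 − m)/7.

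With no true effect and m = 2, the spurious shift is 2d/7: 2.9, 4.3 or 5.7 points for d = 10, 15 or 20.

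With d = 15 and r = 15%:

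| m of 7 | As written | Matched workload |
| --- | --- | --- |
| 1 | 15(1 − 3.15)/7 = −4.6 | −2.25 × 20/7 = −6.4 |
| 2 | 15(2 − 3.15)/7 = −2.5 | −2.25 × 19/7 = −6.1 |
| 3 | 15(3 − 3.15)/7 = −0.3 | −2.25 × 18/7 = −5.8 |

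The mean as written reaches zero at r = m/21: 4.8% for one such patient, 9.5% for two and 14.3% for three. With 5 patients, two of whom change step, the mean as written is (3 × −6.75 + 2 × 8.25)/5 = −0.75, against (3 × −6.75 + 2 × −4.5)/5 = −5.85 when matched.

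**The case against.** The best defence is that the Protocol prescribes 2, 4 and 6 W for all patients. Read literally, end-exercise is the end of the 6 W step at both visits, and the comparison is already matched. A patient who stops at the same step both times also causes no distortion. This stands: unequal steps are a reasonable expectation in this population, not something that the Protocol reports.

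A reader might infer several stronger things that the text does not support.

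- *That the plan deliberately reads depletion at whatever load was reached, and scores an improved patient as worse.* The Protocol says neither. It states no direction of benefit for total depletion, and a reversal from 4 W to 6 W needs a true improvement below about one third.
- *That one or two patients will cancel or create the group result.* In the example with a 15% improvement, two of seven shrink the mean but leave its direction intact. Two cancel it only when the true improvement is about 9.5% or less. No variability figure is given, so it cannot be said that a shift of 2.9 to 5.7 points would create a finding.
- *That Aim 4 rests on this measure.* The Protocol links mitochondrial function to the time constants. Both these and the steady-state differences are estimated per increment, so they can be compared at equal load. That safeguard is not complete: fits with r² below 0.4 are treated as weak, and total depletion is the only depletion measure normalised to rest rather than to the preceding step.

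It can also be said that handling of uncompleted steps belongs in an analysis plan that is not shown here. That would be fair for a missing-data rule. The definition of the measure, however, is fixed in the Protocol and leaves the workload open.

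Finally, end-exercise PCr over resting PCr is strictly the fraction remaining. The fraction hydrolysed is its complement and carries the same information, so this is a matter of labelling.

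**Conclusion.** The definition of total PCr hydrolysis is not tied to a workload. The before/after change in this measure is therefore confounded with work done whenever a patient completes a different number of steps at the two visits. In that case a modest true improvement can be masked. From 4 W to 6 W the sign reverses for an individual if the true per-step improvement is below about one third (31 to 33% across the two depletion models tried). If all patients complete the same steps at both visits, there is no distortion.

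The sizes rest on assumed falls per step, an assumed treatment effect and an assumed number of patients who change step. None of these is in the Protocol. The point affects one subsidiary MRS measure in a small pilot, and the per-increment measures remain usable. It is minor, and worth correcting because the correction is cheap.

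**What to change.** Replace the sentence that defines total PCr hydrolysis with wording such as:

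> The extent of PCr hydrolysis is 1 minus the ratio of the PCr integral at the end of the highest workload completed at both visits to the resting integral of the same session.

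Report the highest workload completed at each visit alongside it, so that a change in exercise tolerance is visible in its own right. The *1 minus* form also settles the labelling.

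The change is to wording only. Each spectrum takes 10 s to acquire and fits are already made for every increment, so no new data are needed. The cost is small: a step completed at only one visit does not enter this measure, and a patient with no step completed at both visits contributes no value to it.

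### The r² cut-off of 0.4 mainly reflects how large the PCr change is relative to noise, so it cannot separate a steady state from progressive PCr breakdown

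*Protocol*

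**What the plan says.** The section Phosphor 31 Magnetic Resonance Spectrosopy plans exercise "during an incremental exercise protocol at 2, 4 and 6 W" and uses the PCr time constants to quantify mitochondrial function. Aim 4 compares muscle energy metabolism at baseline and study endpoint.

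Under 31P MRS Data Analysis, the time constant and the PCr change "are calculated for each workload increment by using a non-linear regression analysis in SPSS 15.0 for windows". Equation (2) is a monoexponential approach to a plateau, with "PCrss the difference between baseline PCr value and the estimated steady-state level". The starting value is a single data point: "the last PCr integral of the preceding increment or rest phase is considered baseline PCr integral for the following increment". Fit is measured by "r2 = 1 - residual sum of squares / corrected sum of squares (3").

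Two readings follow. "A coefficient r2 above 0.4 is considered an acceptable fit", and below that value the same sentence says that "a coefficient r2 below 0.4 indicated a weak agreement with a monoexponential model and rather progressive PCr breakdown". The section sets no condition on the size of the PCr fall, the noise, or the size or precision of the time constant. It does not say what happens in the before/after comparison to increments below 0.4.

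**The concern.** r² is used here for two purposes: as a quality check on the time constant, and as a physiological statement that PCr keeps falling. It suits neither. Its denominator is the total variation of PCr within the increment, so r² depends on signal size as much as on curve shape.

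- **Small change.** If PCr hardly moves, the total variation is mostly noise. r² is then low even if the curve is exactly monoexponential and has reached its plateau. The protocol reads this as progressive breakdown.
- **Steady fall.** As the time constant grows, equation (2) tends to a straight line. A fall that never levels off therefore fits well, passes the cut-off, and yields a time constant the data cannot determine.

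At stake is how the fits behind aim 4 are read. With 5–7 patients, a few mislabelled increments matter.

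**Working it through.** The protocol gives no derivation of 0.4, so there is no figure to reproduce. The rule can be tested against equations (2) and (3).

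**Inputs from the protocol:** one spectrum per 10 s ("10 averages; acquisition time (TA), 10 s"), a separate fit per increment, a single-point baseline, and the cut-off of 0.4. **Assumptions, not in the protocol:** increment length T = 180 s, true time constant τ = 40 s, noise SD s of 1–5% of baseline PCr. Other values are noted where used.

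**Step 1: approximation.** Let V be the variance of the true PCr curve over the increment. If the model can follow the curve, r² ≈ V/(V + s²). Setting this to 0.4 gives V = (0.4/0.6)s² = 0.667s².

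- Straight-line fall D: V = D²/12, so the cut-off lies at D = s√(0.667 × 12) = 2.83s.
- Monoexponential fall A: V/A² = (τ/2T)(1 − e^(−2T/τ)) − [(τ/T)(1 − e^(−T/τ))]² = 0.1111 − 0.0483 = 0.0628. The cut-off lies at A = s√(0.667/0.0628) = 3.26s.

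Both shapes cross 0.4 at a fall of about three noise SDs. The cut-off separates small from large falls, not plateau from no plateau.

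**Step 2: numbers put in.**

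- Monoexponential 5% fall: V = 0.0628 × 25 = 1.57. At s = 1%, r² ≈ 1.57/2.57 = 0.61. At s = 3%, r² ≈ 1.57/10.57 = 0.15.
- Straight line at s = 3%: a 20% fall gives 33.3/42.3 = 0.79, a 30% fall 75/84 = 0.89.

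**Step 3: simulation** of the least-squares fit with the single noisy baseline point. Ranges span separate runs that differ in fitting details.

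| True curve | Noise 1% | 2% | 3% | 5% |
| --- | --- | --- | --- | --- |
| Monoexponential, 5% fall: r² < 0.4 | 11–12% | 74–82% | 92–96% | 99% |
| Monoexponential, 10% fall: r² < 0.4 | 0% | 6–12% | 43–55% | 87–91% |
| Straight line, 20–30% fall: r² > 0.4 | about 100% | about 100% | 99.6–100% | 79–99% |

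- A flat trace gives r² < 0.4 in about 100% of fits (91–100% over increments of 120–300 s, noise of 2% and 4%, and fixed or free baseline).
- Monoexponential falls of 20–30% are mislabelled in only 0–1% of fits at 2–3% noise.
- For straight-line falls of 20–30% at 1–3% noise, the fitted time constant exceeds the increment in roughly 80–100% of fits.
- Without noise, a straight line gives r² of 0.965–1.000, and even an accelerating fall gives 0.74–0.95.
- A small steady fall also fails (straight line, 5% fall, 4% noise: 85–100% below 0.4). The label is then right only by chance.

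**The case against.** Four points on the other side carry weight.

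1. **No exclusion is stated.** A reader might infer that increments below 0.4 lose their time constant, so that few patients keep a usable before/after pair. The protocol does not say this, and a count of lost pairs would describe a step it does not contain. Handling of poor fits may also be left to a statistical analysis plan that is not shown.
2. **The overall response is measured without r².** Total PCr hydrolysis is taken from the end-exercise and resting integrals, so a change in the overall fall would still be seen.
3. **The small-fall rates rest on undocumented inputs.** Noise, increment length, time constant and expected fall are all absent. With low noise or large falls, that error nearly disappears.
4. **A link to treatment is not shown.** It is tempting to argue that, if rhuEPO works, PCr falls less, r² drops and improved patients are called worse. That needs falls small enough to be dominated by noise, and the protocol gives no expected fall or effect. A small fall could also reflect low effort or poor signal rather than good muscle.

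These limit the consequence, not the error. A flat trace is not breakdown whatever its cause. The acceptance of steady falls hardly depends on the assumed noise up to 3%. The protocol cites earlier reports for the method, but earlier use does not change what equations (2) and (3) imply.

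**Conclusion.** The stated rule is wrong on the protocol's own equations. r² below 0.4 does not indicate progressive breakdown, and r² above 0.4 does not show that the time constant is estimable. The flat-trace and steady-fall results held in every variant tried. The rate for small true falls cannot be fixed from the protocol: for a 5% fall it runs from about 11% at 1% noise to 96% at 3%, under the assumed 180 s and 40 s.

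Severity is moderate to minor. MRS is an additional aim of a non-randomised pilot, no exclusion of low-r² increments is stated, and fit-free hydrolysis is already planned. Neither a loss of patient pairs nor a bias tied to the treatment effect is established.

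**What to change.** - Remove 0.4 both as a physiological label and as an acceptance rule.
- Report the observed PCr fall for every increment whatever its r², alongside the planned total hydrolysis.
- Report each time constant with its standard error or confidence interval. Treat it as not estimable when the interval is unbounded or the estimate exceeds the increment length.
- Call an increment progressive breakdown only if PCr has fallen by clearly more than the noise and is still falling at the end, for example an end-increment slope whose confidence interval excludes zero. Otherwise call it indeterminate.
- State how not-estimable and indeterminate increments enter the before/after comparison.

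Two simpler substitutes are not enough. Labelling breakdown whenever a straight line fits better by AICc, or the time constant exceeds the increment, still mislabels about 45% of true monoexponential 5% falls at 3% noise. Switching to 1/τ trades one instability for another, because the fitted time constant is below 5 s in about 19% of those fits.

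The cost is a few sentences and output from the same data and software. The downside is that some increments will be reported as indeterminate.

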**Statistical analysis**

Depending on the distribution of variables (analyzed by the Kolmogorov-Smirnov test) parametric (i.e. one-way analysis of variance (ANOVA); Pearson’s correlation coefficient for univariate correlation analyses) or non-parametric tests (Kruskal-Wallis test; Mann-Whitney-U test for group comparisons, Spearman’s correlation coefficient for univariate correlation analyses) will be used. Multivariable linear regression analysis, controlling for possible confounding covariates, will be performed for the variables found to be significant in the univariate models. Categorial variables will be analysed by chi-square test and logistic regression analysis.

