**Study Design**

This is a single centre, non randomized pilot study.

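### The Kolmogorov-Smirnov pretest that selects the tests cannot work with 5 to 7 patients, and neither branch it leads to names a paired test

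*Protocol*

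**What the plan says.** The Statistical analysis section of the protocol sets the rule: "Depending on the distribution of variables (analyzed by the Kolmogorov-Smirnov test) parametric" methods (one-way ANOVA, Pearson correlation) apply, or else "non-parametric tests (Kruskal-Wallis test; Mann-Whitney-U test for group comparisons", with Spearman correlation. No significance level is given for the pretest, and no Lilliefors correction is mentioned. Multivariable regression then "will be performed for the variables found to be significant in the univariate models", so the outcome of the selected test has consequences further on.

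The design is described thus: "This is a single centre, non randomized pilot study". No control arm appears. The comparison is within patients: "Skeletal muscle will be obtained by an open biopsy from at baseline (untreated) and after 2 months of rhuEPO treatment".

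The section Number of patients gives a range of 5 to 7. Patients and Investigations says: "Seven adult subjects with definite FRDA will be enroled in this study". Neither place says how the two statements relate.

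The only software named is for the spectroscopy curve fit ("non-linear regression analysis in SPSS 15.0 for windows"). The protocol does not say which form of the Kolmogorov-Smirnov test is meant.

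**The concern.** A pretest is useful as a gate only if it can tell suitable from unsuitable data. Here it sees 5 to 7 values per variable and time point. Many endpoints are cell counts, densities, enzyme activities or time constants, for which right skew is plausible. If the pretest can hardly reject, such variables go to the parametric branch on the raw scale whatever their shape. The analysis is then formally data-dependent without the protection that was the reason for the rule.

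The branches have a defect of their own. One-way ANOVA, Kruskal-Wallis and Mann-Whitney, as listed, compare independent groups, whereas the question is the change between week 0 and week 8 in the same people. Even a perfect gate would lead to a test that ignores the pairing.

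**Working it through.** The plan gives no calculation to reproduce, so the check is of how the rule behaves.

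**Inputs.** From the protocol: n = 5 to 7, one group, two time points. Assumed, because the protocol is silent: a two-sided 5% level, and log-normal data with log SD 0.5 (moderate skew) or 1 to 1.5 (strong skew).

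**Step 1: one extreme outlier, by hand.** Take n − 1 equal values and one far away. Coded 0 and 1, the mean is 1/n and the SD is 1/√n, so the equal values stand at z = −1/√n and D = (n − 1)/n − Φ(−1/√n).

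- n = 5: 0.800 − 0.327 = 0.473; standard exact critical value 0.563: not rejected.
- n = 6: 0.833 − 0.342 = 0.492 (unrounded inputs); critical value 0.519: not rejected.
- n = 7: 0.857 − 0.353 = 0.504; critical value 0.483 exact, 0.513 asymptotic: rejected only with the exact value.

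So at n = 5 and 6 the standard test passes even this sample as normal.

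**Step 2: rejection rates by simulation** (at least 200,000 samples per cell; D against a normal with estimated mean and SD; repeat runs differ by a few tenths of a percentage point).

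| n | Log SD | Standard K-S, exact critical value | Lilliefors |
|---|---|---|---|
| 5 | 0.5 | 0% | 9% |
| 5 | 1 | 0% | 20% |
| 5 | 1.5 | 0% | 32% |
| 6 | 0.5 | 0% | 11% |
| 6 | 1 | 0% | 26% |
| 6 | 1.5 | 0% | 42% |
| 7 | 0.5 | below 0.01% | 13% |
| 7 | 1 | 0.1% | 31% |
| 7 | 1.5 | 1.2% | 50% |

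With the asymptotic critical value every standard rate is 0%. Pooling the two time points would not rescue the standard test: even 14 independent values, which these are not, give at most 26% (log SD 1.5, exact value).

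**Step 3: what is lost, and to what.** Power at n = 7, under assumed variances:

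| Between-patient log SD / mean log rise / SD of log ratio | Raw ANOVA | Mann-Whitney | Paired t, raw | Paired t, log |
|---|---|---|---|---|
| 0.6 / 0.6 / 0.5 | 22% | 21% | 49% | 75% |
| 0.3 / 0.3 / 0.3 | – | – | 53% | 60% |
| 0.2 / 0.3 / 0.3 | – | – | 56% | 60% |

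In the first row the two named branches differ by one point. From 22% to 75% is 53 points: pairing brings 49 − 22 = 27 and the log scale a further 75 − 49 = 26. In the other rows the log scale adds 7 and 4 points.

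**Step 4: limits of an exact signed-rank test.** The smallest two-sided p is 2/2ⁿ: 0.0625 at n = 5, 0.031 at n = 6, 0.016 at n = 7. At n = 5 the widest exact interval covers 1 − 0.0625 = 93.75%, so no exact 95% interval exists.

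**The case against.** The case for leaving the plan alone has several parts.

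- *The form of the test is not stated.* This stands. If the Lilliefors version is meant, it is wrong to say that the pretest almost never rejects: strong skew is found in 20% to 50% of samples. That is still a miss at least half the time.
- *The gate does not cause the power loss.* This stands. A reader might take 49% against 75% as the price of the gate. Both figures belong to paired t-tests that the protocol does not name, in one assumed scenario. The branches it does name perform about equally there.
- *The signed-rank limit is not the plan's limit.* This stands. One might infer that with five patients the plan's rank route can never reach significance. The protocol names Mann-Whitney, whose smallest two-sided p at 5 against 5 is 2/252 = 0.008. The signed-rank limit matters only for the replacement.
- *Testing the variables is right for the tests listed.* ANOVA and Pearson do concern the values themselves. The distribution of within-patient changes becomes the relevant one only once a paired analysis is adopted.
- *Seven lies within 5 to 7.* The statements can be read as target and range, so the inconsistency is mild, and nothing shows that either figure is wrong.
- *It is a pilot without a stated power claim.* True, but the protocol still uses significance to choose variables for regression, and the gate decides which test supplies it. The rule is written in the protocol, so it is not a matter merely left to a statistical analysis plan.

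**Conclusion.** The point holds in this form: the pretest does not function as a gate at 5 to 7 patients. With standard critical values it practically cannot reject, at most 1.2% in the log-normal cases tried. With the Lilliefors correction it overlooks strong log-normal skew in 50% to 80% of samples. Neither branch uses the pairing that the design provides. The 5% level and the log-normal shapes are assumptions; the sample size and the rule are the protocol's own.

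No definite loss of power can be attached to the rule, because the protocol gives no variances. The change is worth making, but the weakness does not by itself invalidate the trial.

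**What to change.** In the Statistical analysis section, delete the Kolmogorov-Smirnov rule for the pre/post comparisons and fix one analysis per endpoint: the within-patient change from week 0 to week 8, with a paired t-test and 95% confidence interval.

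- Log scale for positive, right-skewed measures: frataxin, capillary density, enzyme activities, time constants.
- For CD34+ and CD133+ counts in muscle, which may be zero in the 1 mm² counted (the protocol's own background reports low numbers in controls): the log scale with a stated rule for zeros, or a raw or square-root change.
- Raw scale for pH and SARA.
- Exact signed-rank test as sensitivity analysis, with a note that with five pairs it cannot reach two-sided p < 0.05 and gives no exact 95% interval.

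In Number of patients, state whether seven is the target and five the minimum, in agreement with Patients and Investigations.

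The cost is a few sentences, with no patients beyond the seven already mentioned and no further procedures. The small downside is that a parametric scale is fixed before the data are seen; the signed-rank analysis is there to check it.
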